# Periprostatic Nerve Block During Transperineal Prostate Biopsy Under General Anaesthesia: Protocol for a Multicentre Pilot Randomised Controlled Trial

**DOI:** 10.3390/cancers18081251

**Published:** 2026-04-15

**Keywords:** anaesthesia, periprostatic nerve block, post-operative pain, prostate biopsy, prostate cancer, randomised controlled trial, visual analogue scale

## Abstract

Transperineal prostate biopsy is commonly used to diagnose prostate cancer and is usually performed under general anaesthesia only in Australia. Many men experience pain after the procedure while recovering. This study is examining whether an additional local anaesthetic injection around the prostate, known as a periprostatic nerve block, can reduce pain after biopsy. While this injection improves comfort when biopsies are performed under local anaesthesia, it is not known whether it provides benefit when the procedure is done under general anaesthesia. Men undergoing transperineal prostate biopsy will be randomly assigned to receive either the nerve block or a placebo injection before the biopsy. Neither the patient nor the treating team will know which injection is given. Pain levels, use of pain relief medication, and any complications will be assessed before discharge. The findings of this study will help determine whether adding a periprostatic nerve block improves recovery and patient comfort after prostate biopsy performed under general anaesthesia.

## 1. Introduction

Prostate biopsy remains the definitive diagnostic test for the diagnosis of prostate cancer. Two approaches are practised: transrectal and transperineal. The transperineal route has emerged as the preferred technique in many centres worldwide because it allows superior apical sampling and markedly reduces post-biopsy sepsis, without compromising cancer detection compared to a transrectal approach [1,2]. Despite these advantages, some studies have reported higher pain scores with the transperineal approach [3,4,5]. Patient-reported pain is influenced not only by the procedure itself, but also by pre-procedural expectations and anxiety [6], highlighting the need for strategies to optimise tolerability.

In Australia, transperineal prostate biopsy (TPPB) is almost exclusively performed under general anaesthesia, and local anaesthesia is not routinely employed. Nevertheless, 30–50% of patients experience post-procedural pain, and approximately 10% reporting severe pain in the immediate post-operative period [7,8]. To mitigate procedural pain, various local and regional anaesthesia techniques have been reported in the current literature. In several international centres TPPB is increasingly performed under local anaesthesia, in which periprostatic nerve blocks (PPNB) form an integral component of the anaesthetic technique to optimise patient comfort and procedural tolerability [9,10].

The PPNB, originally developed for transrectal biopsy, targets the neurovascular bundle between the prostate and seminal vesicles. It can be performed quickly and safely, under direct ultrasound guidance, and carries minimal additional morbidity [11,12]. Multiple studies have shown that incorporating a PPNB during TPPB improves pain scores, reduces procedural discomfort and overall procedure tolerability [6,9,13].

There are no randomised controlled trials evaluating the role of PPNB in the setting of TPPB performed under general anaesthesia. It is biologically plausible that a supplementary periprostatic block could attenuate nociceptive input during biopsy, thereby reducing early post-operative pain, limiting the need for analgesics, and improving the overall recovery experience. Therefore, this multicentre randomised trial has been designed to test this hypothesis and to determine whether PPNB should be incorporated into routine practice for patients undergoing TPPB under general anaesthesia.

## 2. Patient and Methods

### 2.1. Study Design

This is a prospective, multicentre, randomised controlled trial (RCT) designed to evaluate the efficacy of PPNB in men undergoing TPPB under general anaesthesia. Participants will be recruited from three centres in Sydney, Australia: Chris O’Brien Lifehouse, Sydney Adventist Hospital, and Blacktown District Hospital.

The primary objective of this trial is to determine whether the addition of a periprostatic nerve block reduces post-operative pain, measured using a 10-point visual analogue scale (VAS) prior to discharge, in men undergoing transperineal prostate biopsy under general anaesthesia.

The secondary objectives are to evaluate whether the use of a periprostatic nerve block is associated with differences in complication rates compared to placebo, and to assess whether it reduces the requirement for post-operative analgesia.

This study has received ethical approval from the Sydney Local Health District Human Research Ethics Committee (2020/ETH03024) and has been registered with the Australian New Zealand Clinical Trials Registry (ACTRN12621001143819). All procedures will be performed in accordance with the National Statement on Ethical Conduct in Human Research (2018), Good Clinical Practice guidelines, and the principles of the Declaration of Helsinki. Trial conduct will be overseen by the principal investigator at each site, with central coordination by the chief investigator and support from a study coordinator.

At the study conclusion, a formal data analysis will be undertaken to obtain the result of this study. A schematic SPIRIT format of the study design is outlined in Table 1.

### 2.2. Eligibility Criteria

Inclusion criteria

Adults, age ≥ 18 yearsMale patients scheduled for TPPB under general anaesthesiaAbility to provide informed consent

Exclusion criteria

Inability to provide informed consent or is unwilling to participate in this studyKnown allergy or prior anaphylaxis to local anaesthetic agentsReceived locoregional nerve block/anaesthesia within 24 h prior to biopsyUnable to communicate, read or write in English to a level where they are able to understand the study and consent to inclusion

### 2.3. Patient Recruitment and Screening

Potential participants will be identified through private rooms or urology outpatient clinics at the time of their initial consultations. Patients scheduled to undergo TPPB for the investigation of suspected prostate cancer will be screening against the eligibility criteria by the treating urologist or delegated clinical research member.

All eligible patients will be provided with Participant Information and Consent Forms at their initial consultations. Patients will be encouraged to review these documents at home and are not required to make an immediate decision. Informed consent may be provided on the day of the biopsy or at any time prior to the scheduled procedure. During this period, prospective participants may contact the research team by phone or email to address any questions or concerns.

Screening will include a review of medical history, clinical details, and allergy status. Eligible and consenting patients will be assigned a unique study identification number, which will be recorded on all study documentation and electronic medical records (EMR). Enrolled participants will then proceed to randomisation on the day of biopsy.

Participants may withdraw from the study at any time without prejudice to their ongoing care. Withdrawal can be communicated verbally by speaking directly with a member of the research team, or via telephone or email. While participants will be invited to complete a withdrawal form for record-keeping purposes, this is not mandatory; verbal notification will be considered sufficient.

### 2.4. Randomisation

After informed consent, participants will be randomised in a 1:1 ratio to receive either:

Intervention group: PPNB administered with 20 mL 1% lignocaine with 1:100,000 adrenaline (approved for use by the Therapeutic Goods Administration and listed on the Australian register of Therapeutic Goods (ARTG). The ARTG is a register of therapeutic goods that can be lawfully supplied in Australia), injected under ultrasound guidance immediately prior to biopsyControl group: placebo injection with 20 mL sterile 0.9% normal saline, injected under ultrasound guidance immediately prior to biopsy

The randomisation sequence will be computer generated using variable block sizes (2, 4 and 6); stratification will be by site. The allocation sequence will be prepared off-site by a trained study secretary, who will sequentially number and seal opaque envelopes. A box containing the required number of envelopes for use at each site will be made.

On the day of biopsy, a trained scout nurse will remove a sealed envelope from the box outside the operating theatre. The envelope will be opened, and the allocated injectate (PPNB or placebo) will be prepared in an unlabelled syringe of identical appearance. The scout nurse, who is not involved in outcome collection, will remain the only unblinded team member. Patients, surgeons, anaesthetists, and research staff collecting outcome data and performing analysis will remain blinded to allocation.

To reduce error, each envelope box will also contain a randomisation record, to be completed by the scout nurse at each location (Supplementary File S1). This document includes patient details, allocation, and solution preparation instructions, and will remain secured within the envelope box. A flowchart of instructions will also be affixed to each box to support adherence to protocol.

### 2.5. Intervention

All enrolled participants will undergo TPPB under general anaesthesia and will be randomised as outlined earlier. Immediately prior to biopsy, patients will undergo a periprostatic nerve block (intervention arm) or a placebo injection (control arm).

The PPNB will be performed under ultrasound guidance using a spinal needle advanced transperineally to the space between the prostate and seminal vesicles, targeting the neurovascular bundles bilaterally. A total of 20 mL of 1% lignocaine with adrenaline will be administered (10 mL on each side), with local anaesthetic visualised during injection to confirm placement and minimise risk of extravasation.

The placebo injection will consist of 20 mL sterile 0.9% normal saline, delivered using the same technique. Both active and placebo injectates will be prepared by the unblinded scout nurse in unlabelled syringes of identical appearance to maintain blinding.

Following injection, transperineal prostate biopsy will proceed in the standard manner under general anaesthesia. The biopsy template and number of cores obtained will be determined by clinical factors.

Following the procedure, and prior to discharge, each patient will complete a VAS pain score form (Supplementary File S2). A clinical research team member will collect this form and record any additional analgesia administered post-operatively, on the same form.

Risks and Safety

PPNB is a well established and low risk adjunct to prostate biopsy. The most common adverse effects are pain and bruising at the injection site. Uncommon (1 in 1000) risks include nerve block failure, temporary numbness, allergic reaction to lignocaine, and iatrogenic injury to blood vessels, muscles or nerves. Very rare (1 in 10,000) complications include local anaesthetic systemic toxicity, seizures, or anaphylaxis. All injectates used in this study are approved for clinical use by the Therapeutic Goods Administration.

Patients may experience side effects or serious adverse events related to their TPPB, which will be managed as per clinical protocols and treated accordingly. Investigators will make records of any side effects or serious adverse events, as they are relevant to the scope of the study. This is in line with the NHMRC Safety Reporting and Monitoring in Clinical Trials (2016).

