### 2.7. Sample Size

The primary outcome of interest is the between-group difference in the post-procedure VAS scores between the intervention (PPNB) and placebo injection. A meta-analysis of transrectal prostate biopsies demonstrated that PPNB was associated with a considerable reduction in post-procedural pain, with a pooled standardised mean difference of −1.27 (95% CI −1.72 to −0.82) compared with placebo [14]. Although this suggests a large effect size, the analysis also reported significant heterogeneity (I^2^ = 92%), reflecting variability across trials. A separate review of acute pain interventions reported that the minimum clinically important difference ranged from 0.4 to 4.0, with a median of 1.7 on a 10-point VAS [15].

On this basis, the sample size calculation assumed a between-group difference of 1.5 on the VAS, with a pooled standard deviation of 1.75, corresponding to a large effect size (Cohen’s *d* = 0.86). Using a two-sided α of 0.05 and 80% power, the required sample size is 22 patients per group. Allowing for dropout, a total of 50 patients will be recruited (25 per group). The sample size calculation was performed using G*Power v3.1.9.6 [16].

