### 2.8. Data Collection and Management

Baseline demographic and clinical data will be collected from medical records, including age, prostate volume (from pre-operative imaging), and previous prostate biopsies (number and type). Intra-operative data collected include number of cores and duration of procedure.

The primary outcome, post-procedure pain, will be assessed using a 10-point VAS score completed by participants prior to discharge. Secondary outcomes, including type and dose of post-operative analgesia, will be documented by the clinical research team and converted to oral morphine equivalents for analysis. Complications will be recorded prospectively during the admission and retrospectively through review of electronic medical records, with severity graded according to the Clavien–Dindo classification. This is summarised in Table 2.

All outcome data will be entered prospectively (coded) into a secure database hosted by Western Sydney Local Health District. Each participant will be assigned a unique study identification number, which will be used on all study forms and electronic entries. Identifiable information will be stored separately from coded data and accessible only to the principal investigators at each site. Access to the data is password protected and limited to only the named research investigators. Data will be retained for 15 years following study completion in accordance with local NHMRC Code for The Australian Code for the Responsible Conduct of Research. At the end of the retention period, electronic records will be permanently deleted and paper records securely destroyed.

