### 2.9. Statistical Analysis Plan

Descriptive statistics will be presented on baseline characteristics of the two groups. Continuous variables reported as mean (standard deviation) or median (interquartile range), while categorical variables will be reported as frequencies and percentages.

The primary outcome, post-operative pain measured by VAS, will be compared between groups using an independent-samples *t*-test if normally distributed, or a Mann–Whitney U test if non-normally distributed.

Secondary outcomes will be analysed as follows:Post-operative analgesia requirements (oral morphine equivalents) will be compared using *t*-tests or Mann–Whitney U tests, depending on data distribution.Complication rates will be compared between groups using χ^2^ tests or Fisher’s exact tests where appropriate.Procedure duration and number of biopsy cores will be analysed using *t*-tests or non-parametric equivalents.

All statistical tests will be two-sided, with a significance level set at *p* < 0.05. Effect sizes with 95% confidence intervals will be reported for primary and secondary outcomes. Missing data will be handled using complete case analysis. Statistical analysis will be performed using SPSS (Version 29, Armonk, NY, USA).

In the event of significant missing data, a sensitivity analysis will be performed to assess the robustness of these findings.

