### 3.2. Limitations

However, there are some limitations inherent to this study. The modest sample size, powered to detect a clinical difference in early post-operative pain, may limit ability to detect smaller differences in secondary outcomes. Pain is inherently subjective and influenced by patient pain thresholds; in addition, peri-operative anxiety and recovery room factors may introduce variability. Variations in biopsy template, number of cores and subtle inter-operator technique differences across centres may introduce heterogeneity, although this reflects real-world practice.

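### Core number and procedure duration are tested as secondary endpoints that no objective supports, and the valid but unadjusted primary VAS comparison may give up some precision

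*Protocol article*

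**What the plan says.** All references are to the protocol article.

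- **Section 2.5, Intervention:** "The biopsy template and number of cores obtained will be determined by clinical factors".
- **Section 2.6, Endpoints, and section 2.9, Statistical Analysis Plan:** procedure duration and core number share one line of the secondary endpoints. Both are compared between arms by t-tests or non-parametric equivalents, two-sided at 5%.
- **Section 2.1, Study Design:** the secondary objectives cover complications and post-operative analgesia only.
- **Table 2:** cores and duration stand in the intra-operative domain. The secondary-outcome domain holds only analgesia use and complications.
- **Section 2.9, primary outcome:** "post-operative pain measured by VAS, will be compared between groups using an independent-samples" t-test, or by Mann–Whitney U if the scores are not normal. No covariate and no site term appears.
- **Section 2.4, Randomisation:** allocation is stratified by site, and surgeons are blinded.
- **Section 2.8, Data Collection:** baseline data include "age, prostate volume (from pre-operative imaging), and previous prostate biopsies (number and type"). Table 2 adds PSA. Core number is recorded during the procedure.
- **Section 3.2, Limitations:** "Variations in biopsy template, number of cores and subtle inter-operator technique differences across centres may introduce heterogeneity".

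**The concern.** There are two linked points.

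First, the article does not agree with itself on whether cores and duration are outcomes. An endpoint tested at 5% should answer a stated question, and here there is none. For cores, the design also gives little reason to expect a response to allocation: the surgeon is blinded, the patient is under general anaesthesia, and the number follows clinical factors. A p-value below 0.05 would invite a causal reading that the design does not support.

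Second, the article names technique and centre differences as possible sources of heterogeneity, stratifies by site and collects baseline variables, but its primary comparison uses none of this. In a trial of 50, a prognostic covariate named in advance can narrow the interval for the VAS difference at no cost in patients. What is at stake is efficiency, since power at the stated 22 per arm is already close to 80%.

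**Working it through.** **Endpoint status.** Sections 2.6 and 2.9 treat cores and duration as outcomes; section 2.1 and Table 2 do not. Section 2.5 adds that cores depend on clinical factors. These places need reconciling, and no arithmetic is involved.

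**Inputs from the documents.** Section 2.7: "the sample size calculation assumed a between-group difference of 1.5 on the VAS", "with a pooled standard deviation of 1.75". Section 2.4: "participants will be randomised in a 1:1 ratio". The stated result in section 2.7: "Using a two-sided α of 0.05 and 80% power, the required sample size is 22 patients per group".

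**Stated figure reproduced.** d = 1.5/1.75 = 0.857.

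- Normal approximation: n = 2 × (1.960 + 0.842)² / 0.857² = 21.4, so 22 per arm.
- Exact noncentral t: noncentrality = 0.857 × √(22/2) = 2.843 on 42 df, power 79.3%. The exact requirement is 23 per arm. Power at 25 per arm is 84.4%.

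The stated 22 is reproduced to within one patient per arm, so I take 79.3% as the unadjusted reference.

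**Effect of adjustment.** For k covariates that explain a share R² of within-arm VAS variance, with N patients analysed:

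SE ratio = √[(1 − R²) × (1 + k/(N − k − 3))]

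The second factor is the price of estimating the covariates and of their chance imbalance. Power uses noncentrality 2.843 / ratio on N − 2 − k df. R² is an assumption throughout. The 95% half-width is t × 1.75 × √(2/22) × ratio; unadjusted it is 2.018 × 0.528 = 1.06 VAS points.

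Two covariates, N = 44, second factor 1 + 2/39 = 1.051, 40 df:

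| Assumed R² | SE ratio | Power | 95% half-width |
|---|---|---|---|
| 0 | 1.025 | 77.2% | 1.09 |
| 5% | 0.999 | 79.3% | 1.07 |
| 10% | 0.973 | 81.4% | 1.04 |
| 15% | 0.945 | 83.5% | 1.01 |
| 25% | 0.888 | 87.8% | 0.95 |

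Break-even is where (1 − R²) × 1.051 = 1, so R² = 4.9%.

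**With site added.** Three centres need two more terms, so k = 4. The second factor is 1 + 4/37 = 1.108, and break-even is 1 − 1/1.108 = 9.8%, about 10% in total. This errs on the cautious side, because the formula charges site for chance imbalance that stratified blocks largely prevent.

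**Cross-check.** A simulation with one covariate at 22 per arm (10,000 runs per value) gave adjusted power of 77.9%, 78.7%, 80.5%, 82.3% and 88.0% at correlations with VAS of 0, 0.1, 0.2, 0.3 and 0.5, against 79–80% unadjusted. The pattern is the same: nothing gained below a correlation of about 0.15–0.2, a modest gain at 0.3, a material one at 0.5.

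**Chance imbalance.** With 25 per arm, the standardised difference in a covariate has SD √(2/25) = 0.283.

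- Above 0.3 SD: probability 29%. At correlations of 0.3–0.4, a 0.3 SD imbalance moves the VAS difference by 0.3 × (0.3 to 0.4) × 1.75 = 0.16–0.21 points, 11–14% of the 1.5 target.
- Above 0.4 SD: probability 16%. A 0.4 SD imbalance gives 0.21–0.28 points, 14–19% of the target.

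**The case against.** The strongest reply is that nothing here is an error of inference. A randomised two-sample comparison is unbiased, and its standard error already allows for chance imbalance. An unadjusted primary test is a legitimate choice in a 50-patient trial titled a pilot, and a fuller analysis plan might add an adjusted analysis. All of that stands, except that section 2.9 does fix the unadjusted test as the primary one.

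The gain is also not documented. No covariate–VAS correlation is given, and section 3.2 says only that core number may introduce heterogeneity. The patient-level pain drivers named in the Discussion and in section 3.2 (pain threshold, expectations, anxiety) are not among the baseline variables. This stands, and it is why the gain is shown as a range that includes a loss.

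Core number as the protocol records it is known only after randomisation and injection, so it is not a clean covariate. This stands; only a planned number fixed beforehand would qualify.

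The distribution matters too. The Introduction puts post-procedural pain at 30–50% of patients, so many scores may lie near zero. The normal-theory power figures are therefore approximate, which is a reason to keep the unadjusted comparison, with its rank-based option, alongside the model.

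Finally, comparing cores and duration by arm is a reasonable check of procedure conduct. A descriptive comparison serves that purpose without a test.

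**Conclusion.** The point holds as one of endpoint classification and efficiency. Listing and testing cores and duration conflicts with the article's objectives and Table 2. For cores, a significant difference would most plausibly be chance.

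A reader might go further in three ways that the documents do not support:

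- **That a core difference could only be chance.** Section 2.5 says clinical factors determine the number, not that it is fixed before the injection.
- **That the unadjusted VAS comparison is biased or invalid.** It is neither.
- **That precision is certainly lost, and that cores obtained should be the covariate.** The loss depends on an undocumented R², and cores obtained is a post-randomisation variable.

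The size, at SD 1.75, difference 1.5, 22 per arm, a linear relation and two covariates, is a change in power of about −2 points at R² = 0, none near 5%, and +2, +4 and +8 to +9 points at 10%, 15% and 25%. Once site is included, about 10% of variance must be explained before anything is gained. At the full 25 per arm, unadjusted power is already 84.4%, and two covariates at R² = 10% give 86.4%.

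**What to change.** 1. Take core number and procedure duration out of the secondary endpoints in section 2.6 and out of the tests in section 2.9. Report both descriptively by arm as data on procedure conduct, in line with section 2.1 and Table 2.
2. Make the primary estimate the arm difference in VAS points, with its 95% confidence interval, from a linear model with site and one or two pre-randomisation covariates. Name them before any unblinded data are seen. Age or prostate volume are candidates already collected. Planned core number is another, provided it is recorded before the envelope is opened. Do not adjust for cores obtained.
3. Keep the unadjusted comparison of section 2.9 as a supportive analysis.

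The first change costs only wording. The second costs one degree of freedom per covariate and two for site, plus one pre-operative field if planned core number is chosen. If two covariates turn out to explain nothing, the standard error rises by about 2.5% at 22 per arm. With site also in the model and also explaining nothing, the cautious formula gives √1.108 = 1.053, a rise of about 5%. That is the reason to restrict the list to variables for which the investigators can argue a relation with pain.

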### 2.6. Endpoints

Primary endpoint

Post-operative pain: measured using a 10-point visual analogue scale completed by the participant prior to discharge following TPPB. This is approximately 3–4 h post general anaesthesia, reflecting standard hospital protocols, resulting in a consistent and comparable timeframe across study participants.

Secondary endpoints

Post-operative analgesia requirements, recorded as type, route, and dose, converted to oral morphine equivalentRate and severity of complications arising from use of PPNBProcedure duration and number of biopsy cores obtained

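### A null result on the single pre-discharge VAS, compared without regard to analgesia given before it, cannot by itself show that the block is unnecessary

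*Protocol article*

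**What the plan says.** Section 2.6 defines the primary endpoint as pain "measured using a 10-point visual analogue scale completed by the participant prior to discharge following TPPB", and adds: "This is approximately 3–4 h post general anaesthesia, reflecting standard hospital protocols". Tables 1 and 2 list no other pain score.

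On analgesia, Section 2.5 states: "A clinical research team member will collect this form and record any additional analgesia administered post-operatively, on the same form". Section 2.6 makes analgesic requirement a secondary endpoint, recorded by type, route and dose and converted to oral morphine equivalents. Table 2 gives the medication chart as its source.

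The analysis in Section 2.9 is a two-group test: "The primary outcome, post-operative pain measured by VAS, will be compared between groups using an" independent-samples t-test, or a Mann–Whitney U test if the data are not normal. Analgesic use is tested separately in the same way. The article links the two neither in the analysis nor in the interpretation.

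Two other places bear on this. The Introduction (Section 1) expects the block both to reduce early pain and to limit analgesic need. The Conclusions (Section 4) say that a null finding would suggest that the extra injections are not needed.

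**The concern.** Under the trial's own hypothesis, analgesia during the 3–4 h before the score is a consequence of treatment. If men are medicated because they hurt, more controls than block patients are medicated, and their later VAS is lower than it would have been. A man at 2/10 after an opioid then counts the same as a man at 2/10 with nothing. The primary endpoint loses signal just as the secondary endpoint gains it.

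At stake is the interpretation. Equal VAS scores reached with more analgesia in controls would be a benefit of the block, yet the Conclusions would class that result as evidence against it. The limitations in Section 3.2 do not mention this. They do concede limited ability to detect smaller differences in secondary outcomes, so the analgesic comparison cannot be counted on to correct the reading.

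**Working it through.** **Step 1: the plan's own figure.** Section 2.7 states that "the sample size calculation assumed a between-group difference of 1.5 on the VAS, with a pooled standard deviation of 1.75", and: "Using a two-sided α of 0.05 and 80% power, the required sample size is 22 patients per group". With 1:1 allocation (Section 2.4), d = 1.5/1.75 = 0.857. The normal approximation gives 2 × (1.960 + 0.842)² / 0.857² = 21.4, so 22 per group, which matches. The exact noncentral t gives 22.4, so 23; power is 79.3% at 22 per group and 84.4% at the 25 to be recruited. The sample size is not in dispute.

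**Step 2: direction, by simple arithmetic.** Observed difference = 1.5 − (excess share medicated in controls × VAS drop from analgesia). The article gives neither term, so both are assumed. Power is at 22 per group with the SD held at 1.75.

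| Excess share medicated | VAS drop | Observed difference | Power |
|---|---|---|---|
| 0 | any | 1.5 | 79% |
| 0.10 | 1 | 1.5 − 0.1 = 1.4 | 74% |
| 0.20 | 2 | 1.5 − 0.4 = 1.1 | 53% |
| 0.30 | 2 | 1.5 − 0.6 = 0.9 | 38% |

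Every case with more analgesia in controls moves towards zero. Holding the SD fixed overstates the loss of power, because treating the men in most pain also narrows the spread.

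**Step 3: simulation that lets the spread shrink.** Assumptions: pain before analgesia is normal with mean 3.5 (control) and 2.0 (block), SD 1.75, clipped to 0–10. A man is medicated if his pain is at or above a threshold, and analgesia cuts his VAS by a fixed percentage. The test is the t-test with 22 per arm. Clipping makes the latent difference about 1.4, and power with no analgesic effect is about 79%. Where two powers are shown, repeated runs differed by that much.

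| Threshold | Medicated, control v block | 30% cut | 50% cut | 70% cut |
|---|---|---|---|---|
| 3 | 61% v 28% | 0.91; 77% | 0.58; 62% | 0.25; 19% |
| 4 | 39% v 13% | 0.98; 75% | 0.70; 58% | 0.42; 25% |
| 5 | 20% v 4% | 1.13; 76% | 0.95; 65–67% | 0.77; 47–49% |

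Each cell gives the observed difference, then power. A 30% cut costs only 2 to 4 points of power, but the estimate still falls from about 1.4 to between 0.91 and 1.13. A 70% cut costs much more.

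**Step 4: would a joint measure recover the signal?** In the same simulation, a rank rule that places any medicated man below any unmedicated man holds about 76–78% power at threshold 4, whatever the cut. A Silverman-type sum of ranks (analgesia as yes/no) holds roughly 70% or more. Both are flattered by medication being an exact function of pain. If 20% or 40% of men also receive analgesia unrelated to pain, the rank rule falls to about 64% and 57%. Raw VAS has 79% with no analgesic effect and 75% at a 30% cut.

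**The case against.** The strongest reply is that nothing is biased. Section 2.1 sets the objective as pain on a VAS before discharge. That is a legitimate question under usual care, and the planned test answers it. If the block does nothing, this mechanism produces no false difference. This stands. A reader might infer that the primary comparison is invalid, and the article does not support that.

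Second, analgesic use is already collected, converted and compared with a confidence interval, so a sparing effect could appear there. This stands in part: no joint reading is stated, and Section 3.2 concedes limited power for secondary outcomes.

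Third, a reader might infer that analgesia is unrestricted and that VAS and analgesic timing could never be linked afterwards. Neither is established. The article states no restriction, but the full protocol may contain one. The medication chart and the VAS form (Supplementary File S2) are not shown and may carry times.

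Fourth, the size is wholly assumed. A control mean of 3.5 with SD 1.75 lies 3.5/1.75 = 2 SD above zero, so nearly every control has some pain, whereas the Introduction reports pain in 30–50% of patients. This stands, and it is why a range is given.

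Fifth, replacing the primary endpoint with a composite would be a trade-off and not a clear gain. Step 4 bears this out.

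**Conclusion.** The point holds as one of interpretation and attenuation. If the block works and analgesia is given in response to pain, the VAS difference shrinks. With a latent difference of about 1.4 and 22 per arm, it falls to between about 1.1 and 0.25, with power from about 77% to 19%. Those limits depend on assumed thresholds and analgesic responses; the loss is negligible if analgesia is rare, weak or balanced between arms. It would go too far to say that analgesics will hide the effect. What the documents do support is that a null VAS result alone does not justify the statement in the Conclusions that the injections are unnecessary. This is a cheap improvement to the plan and does not call for a new primary endpoint.

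**What to change.** 1. Keep VAS as the primary endpoint, and state in Section 2.6 that it measures pain before discharge whatever analgesia was given.
2. In Section 2.9, prespecify one named key supportive analysis that combines VAS and oral morphine equivalents for each patient, for example the Silverman integrated rank score.
3. Make sure that the existing form captures the clock time of the VAS and of each analgesic dose. Settle this before or during recruitment, since times not captured on the day may be hard to recover.
4. Amend Section 4 so that a null VAS result is read as showing no benefit only if the joint analysis and the analgesic comparison also show none.

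The cost is one extra analysis, a few form fields and some wording. The composite is harder to interpret than VAS points and loses power if much analgesia is given regardless of pain, so it should support the primary analysis and not replace it. Analgesic care is unchanged.
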